### 123 Establishing whether LAIV impacts the nasopharyngeal microbiome, with a specific focus on the burden of *Streptococcus pneumoniae*

The complex issue of sample size requirements to assess bacterial carriage dynamics in humans following LAIV has received in depth scrutiny in the literature [74] and needs to take into account likely colonization rates in the study population. Sample size calculations have been estimated in the literature using a stochastic-stimulation approach, with variance in carriage density parameterized by data previously collected in the authors' laboratory. Taking into account a likely *S. pneumoniae* carriage prevalence of 80% in the study population [64], a sample size of  $n = 100$  vaccinated children would provide  $\geq 90\%$  power at an alpha of 0.05, to detect a  $\geq 2$ -fold increase in carriage density of *S. pneumoniae* from baseline following LAIV [74]. At a carriage rate of 90%, a sample size of  $n = 230$  (the number of children planned to be given LAIV) would provide  $\geq 80\%$  power at an alpha of 0.05, to detect a 1.5-fold increase in carriage density of *S. pneumoniae*. It has been reported that 1.5 to 2-fold increases in carriage density of *S. pneumoniae* may represent clinically relevant values with respect to a potential for increased transmission of *S. pneumoniae* [74, 75].

## 124 Planned analyses

### 125 Microarray data analysis:

These analyses will be conducted via collaboration with the [name] group (University of Edinburgh), facilitated by collaboration with [name] (University of Sao Paulo) and the MRC statistics and bioinformatics team.

Analyses will be conducted using Perl and Python scripts, R/bioconductor packages, as well as a broad range of tools and databases. Similar methods will be applied to both nasal and blood transcriptome data.

Microarray data will initially be normalized to background values and expression fold change calculated for each gene by comparison of day 2 with baseline values. Non-informative genes will be filtered out at a defined threshold of expression from baseline (e.g. 1.25-fold seen in at least 20% of vaccines [66]). Several independent statistical tests will be performed and only those significant in all tests taken forward for further analysis. Comparison of normalized data between groups (e.g. those with and without a  $\geq 2$ -fold increase in influenza-specific nasal IgA [7]) will utilize linear modeling of the  $\log_2$  scale expression values between groups and subsequent empirical Bayesian statistical testing with vertical p-value adjustment for multiple testing to control for false discovery rate. Pearson's correlation will be used to investigate relationships between fold-expression changes in genes and the magnitude of antibody or T-cell responses to identify probe sets that correlate with an immunological response [66].

Computational network-based approaches such as ingenuity pathway analyses will be used to examine relationships in the data using correlation of gene expression and biological relationships. Several groups have compiled compendia of coordinately expressed modules of genes and can be visualized as nodes linked by connections to other genes with correlated expression level. As such, vaccine responses can be analyzed basis of a number of co-regulated genes rather than individual expressed genes.

Minimum sets of genes capable of predicting an immunological response will be identified via supervised learning classification methods such as Discriminant Analysis via Mixed Integer Programming (DAMIP) [66] and supervised vector machine learning techniques. RT-PCR of identified genes will be used for validation of these findings. Initial analysis will be conducted on phase I collected samples and this dataset used as a training set to identify predictive genes. The predictive accuracy of these classification rules will be tested using phase II collected samples.

Deconvolution meta-analysis of gene expression will be performed on blood transcriptional responses to reveal immune cell type related to the identified sets of genes. Similar analyses will be attempted on nasal transcriptomic data, although this will rely on the availability of *in vitro* epithelial cell microarray data. In addition, the cell types picked up in nasal samples will also be less heterogeneous than in whole blood, with the majority of RNA likely to be from epithelial cells and very little from monocytes, dendritic cells, B and T-lymphocytes.

### 126 Microbiome sequencing:

These analyses will be performed via collaboration with the [name] group (University of Edinburgh), under consultation with the [name] group at the MRC Gambia.

Quality checks will be performed on initial sequencing results to filter reads and fragments of poor quality. Sequences of similar identity will be clustered together to produce OTUs. The relative abundance of each OTU will be calculated. Representative sequences from each OTU will be compared with a reference database to identify genera (and species if sequence

resolution allows). Absolute abundance will also be calculated by combination of relative abundance data with 16s qPCR data.

## **127 Association between microbiome and mucosal response to LAIV**

Several approaches will be taken to explore association between the nasopharyngeal microbiome and response to LAIV. Firstly, a supervised analysis will be performed to compare the relative abundance of the top 20 OTUs between mucosal IgA responders and non-responders, using appropriate parametric or non-parametric analyses (e.g. ANOVA, Kruskal-Wallis test) and *post-hoc* tests to adjust for multiple comparisons.

Secondly, an unsupervised analysis will be performed. Baseline data will be analyzed through Qiime, allowing statistical analyses [76, 77], clustering of data and/or individuals through Unifrac methodology and bacterial network analyses through CoNet analyses (<http://systemsbiology.vub.ac.be/conet>). This methodology allows differentiation of several microbiome 'clusters' or 'profiles', characterized by a particular biomarker species (e.g. *Streptococcus* spp., *Staphylococcus* spp., *Haemophilus* spp. *Dolosigranulum/Corynebacterium* spp. combined profile) [77]. The proportion of IgA responders and non-responders within each cluster or profile can then be calculated.

Finally, univariate and multivariate linear regression models will be used to incorporate microbiome and other factors as predictors of an IgA response.

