**Figure 1. Sample size estimates to detect 2-fold gene expression changes**

## 122 Identifying associations between nasopharyngeal microbiota and nasal and oral influenza-specific IgA responses post-LAIV in Gambian children, to explore whether microbiome variability can explain suboptimal immune responses in some individuals

Calculations were performed using the Shiny application for determining sample size calculations for case-control microbiome studies (<https://fedematt.shinyapps.io/shinyMB/>) [73]. Simulations were run using the anterior nares-derived microbiome data available on the application, estimating that analyses would consider the most abundant 150 operational taxonomic units (OTUs). IgA responders and non-responders were defined as cases and controls respectively and sample size/power calculations performed to detect a 1.5-fold

difference in abundance in the 10 most abundant OTUs and 2-fold difference in abundance in the next 10 most abundant OTUs, between the two groups (Figure 2).

Power calculations were performed using these parameters, for a range of sample sizes from 50 – 150 per group and using the Wilcoxon-Mann-Whitney (WMW) test applied to each OTU individually and the resulting *P*-values multiplicity adjusted with the Benjamini and Hochberg method to control the false discovery rate ('WMWavg' – Figure 3). Prior data suggest that approximately 50% of children receiving LAIV are IgA responders, using a definition of  $\geq 2$ -fold rise in IgA from baseline [7]. At an alpha of 0.05, 82 subjects per group would give a power of 80%. A sample size of  $n = 100$  per group was selected (i.e.  $n = 200$  children given LAIV, accounting for approximately 50% showing an IgA response), which even accounting for some drop outs would give a power of  $\geq 80\%$ .

If required, the complexity of data may be reduced by defining microbiota composition according to 8 distinct profiles described by the [name] group [1] rather than variability across 20 different OTUs/species, thus reducing the need for correction for multiple testing and increasing the power significantly.

[figure not shown]

**Figure 2. Simulations of anterior nares derived microbiome data showing differences between cases and controls of the 20 most abundant OTUs.**

[figure not shown]

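### Primary objective (ii): the responder comparisons do not adjust for day 0 IgA, and the plan does not commit to a regression that does

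*Combined protocol and SAP*

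**What the plan says.** Section 127 lists three approaches and ranks none of them as the main one.

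- The supervised step will "compare the relative abundance of the top 20 OTUs between mucosal IgA responders and non-responders", "using appropriate parametric or non-parametric analyses (e.g. ANOVA, Kruskal-Wallis test"), with post-hoc adjustment for multiple comparisons. No covariate is named.
- The unsupervised step clusters baseline microbiome data and computes the proportion of responders in each cluster. Again no covariate is named.
- Last, "univariate and multivariate linear regression models will be used to incorporate microbiome and other factors as predictors of an IgA response". The other factors are not listed, and the text does not say whether the outcome is day 21 IgA or the rise.

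Section 127 gives no cut-off for response. Section 122, the sample size section for this same objective, uses a rise of at least 2-fold from baseline: "Prior data suggest that approximately 50% of children receiving LAIV are IgA responders" on that definition. Section 125 gives the same rule as an example for the microarray comparison.

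Section 122 sizes the study for a Wilcoxon-Mann-Whitney test on each OTU with Benjamini-Hochberg adjustment. The target is a 1.5-fold "difference in abundance in the 10 most abundant OTUs and 2-fold difference in abundance in the next 10 most abundant OTUs". It then states: "At an alpha of 0.05, 82 subjects per group would give a power of 80" per cent.

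Table 3 lists influenza-specific IgA on the day 0 and day 21 oral and nasopharyngeal samples, so the baseline value is available. No planned analysis names it as a covariate. Section 129 says in general terms that relevant covariates will be considered in all analyses. Section 128, on the reverse question, does name adjusters: recent antibiotic use, age and nutritional status.

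**The concern.** A fold rise contains the baseline value with a negative sign. Children who start low become responders more readily, partly through regression to the mean. Starting IgA is likely to vary in this population: enrolment spans 24 to 59 months, and section 4 reports local exposure by 18 months of 24%, 94% and 93% to the three virus types. A taxon that follows age or past exposure, and so day 0 IgA, can differ between responder classes without having any bearing on the response itself. The sign also misleads: a taxon that goes with high day 0 IgA looks like a marker of non-response. Multiplicity control makes this less frequent but does not remove the bias.

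Cutting a continuous response in two also discards information. Objective (ii) asks whether microbiome variability can explain suboptimal responses, so both an artefact of baseline and a missed association bear directly on its conclusion.

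**Working it through.** **The plan's own figure.** The 82 per group came from simulation on an external anterior nares dataset. The documents give no OTU variances, so it cannot be reproduced. By normal approximation it implies a standardised difference of (1.96 + 0.84) × √(2/82) = 0.44 at a two-sided 5% level, or (3.02 + 0.84) × √(2/82) = 0.60 at 0.05/20 = 0.0025. Nothing here shows it to be wrong.

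**Sample size used.** Groups A and B give 2 × 110 = 220 children. With the 10% attrition of section 51, 220 × 0.9 = 198, or 99 per class at 50% responders, close to the planned 100.

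**Model.** Let X and Y be log IgA at day 0 and day 21, scaled to unit variance, with correlation ρ. The rise is D = Y − X, and the mean rise is set so that half the children respond. An OTU has correlation r with X and no effect on Y given X. Both ρ and r are assumptions.

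**Baseline gap.** corr(X, D) = −√((1 − ρ)/2). Responders therefore start lower by 2 × √(2/π) × √((1 − ρ)/2) SD, which is 0.87 SD at ρ = 0.4 and 0.62 SD at ρ = 0.7.

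**A taxon linked only to baseline.** corr(OTU, D) = −r√((1 − ρ)/2). The expected test statistic is about |corr| × √(2/π) × √198.

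- r = 0.3, ρ = 0.4: 0.164 × 0.798 × 14.07 = 1.84. Chance of p < 0.05: about 45%. At 0.0025: about 12%.
- r = 0.2, ρ = 0.7: 0.0775 × 0.798 × 14.07 = 0.87. Chance of p < 0.05: about 14%. At 0.0025: about 1.6%.

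The 0.0025 level is the first Benjamini-Hochberg step over 20 OTUs.

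**A taxon with a true effect b.** The residual variance of Y is 1 − ρ². For the split, corr(OTU, D) = b/√(2(1 − ρ) + b²). For the regression, the statistic is b√198/√(1 − ρ²).

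- b = 0.15, ρ = 0.4: split 0.136 × 0.798 × 14.07 = 1.52; regression 0.15 × 14.07/0.917 = 2.30. Power at 0.0025: about 7% and 24%.
- b = 0.20, ρ = 0.7: split 0.25 × 0.798 × 14.07 = 2.81; regression 0.20 × 14.07/0.714 = 3.94. Power at 0.0025: about 41% and 82%.

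**Simulation** (Mann-Whitney on responder class against regression of day 21 on OTU plus day 0; n = 198, ρ 0.4 to 0.7, r 0.2 to 0.3, b 0.15 to 0.20):

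| Quantity | Responder split | Baseline-adjusted regression |
|---|---|---|
| Baseline-only OTU flagged, unadjusted 5% | about 11-45% | about 4-6% |
| Same OTU flagged, Benjamini-Hochberg over 20 | about 1-14% | not tabulated |
| Any OTU flagged, one linked taxon | about 6-17% | about 4-7% |
| Any OTU flagged, four linked taxa | about 8-39% | about 4-7% |
| Power for a true effect, Benjamini-Hochberg | about 5-40% | about 23-83% |

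At r = 0.1 a linked OTU is flagged in under 1% of runs after Benjamini-Hochberg. At r = 0 the unadjusted rate is the nominal 4-5%. With 20% assay error variance in IgA (ρ 0.5 to 0.7, r 0.2 to 0.3), the adjusted regression still rejects in about 6-10% of runs at the 5% level.

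**The case against.** The strongest reply is that the plan is not confined to the unadjusted split. Its third approach is multivariable regression, and linear regression suggests a continuous outcome. Section 129 promises relevant covariates throughout. A reader might infer that adjustment for day 0 IgA is ruled out; it is not. This stands. What is missing is a commitment: no covariate list, no stated outcome, and no statement of which approach carries the conclusion. Section 128 shows that the plan names adjusters when it means to.

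Second, the unadjusted 11-45% is not the rate the plan would produce, because section 127 adjusts for multiple comparisons and section 122 names Benjamini-Hochberg. This also stands: the relevant figures are those after adjustment, and they are modest unless several taxa track baseline IgA at around 0.3.

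Third, if response is defined as a fold rise, a taxon tied to baseline is truly correlated with it, and the objective speaks of associations. A reader might infer that the plan would present such taxa as causes. It makes no causal claim. But the objective also asks whether the microbiome explains poor responses, and an association created by the baseline would misinform that.

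Fourth, OTUs are not randomised. Section 10 proposes that commensals influence nasal IgA. If they also shape day 0 IgA, adjustment removes part of the association sought. This is a fair limit on the fix and a reason to show both results.

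**Conclusion.** The point holds as a gap in pre-specification with a measurable cost. The first two analyses for a primary objective leave day 0 IgA uncontrolled, and nothing commits the third to controlling it. Applying the 2-fold rule to section 127 rests on section 122, which serves the same objective.

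The bias depends on assumed correlations. After multiplicity control it is negligible at a taxon-baseline correlation of 0.1. At 0.2 to 0.3 with four linked taxa, the chance of any flagged OTU is about 8-39%. The loss of power does not require any taxon to be linked to baseline: adjusted regression did better throughout the range examined.

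A reader might go on to infer that 82 per group is wrong or that more children are needed. Neither follows: the figure could not be checked from the documents, and the proposed analysis uses the same children.

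**What to change.** In section 127, specify the regression already planned as log day 21 IgA on each OTU, with log day 0 IgA and age as covariates and false discovery rate control across OTUs. State that conclusions on objective (ii) rest on it. Keep the responder comparison as supportive, restate the 2-fold definition there, and report it also adjusted for day 0 IgA, for example by logistic regression. Show the unadjusted result alongside, since adjustment excludes any pathway that runs through day 0 IgA.

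The cost is wording and analysis time; day 0 and day 21 IgA are already to be measured. There are two downsides to state openly. The 82 per group was calculated for the responder comparison, so the plan should say that its stated power refers to what is now the supportive analysis. Assay error in IgA will leave some residual bias after adjustment.

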**Figure 3. Sample size and power estimates to detect differences in the top 20 most abundant OTUs between two groups (1.5-fold difference in the top 10 abundant OTUs and 2-fold difference in the next 10 most abundant OTUs). WMWavg refers to the Wilcoxon-Mann-Whitney test as applied to each OTU and multiplicity adjusted to control for false discovery rate.**

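### Section 127 aims to adjust the 20-OTU responder comparison for multiplicity, but with two groups its post-hoc tests adjust nothing across OTUs, and the Benjamini-Hochberg step behind the sample size is not carried over

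*Combined protocol and SAP*

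**What the plan says.** Primary objective (ii) in section 15 asks whether nasopharyngeal microbiota are associated with nasal and oral influenza-specific IgA responses after LAIV. Two places describe how OTUs will be compared for it.

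- **Section 127 (planned analysis).** The first analysis listed is to "compare the relative abundance of the top 20 OTUs between mucosal IgA responders and non-responders". The tests are to be parametric or non-parametric as appropriate, "e.g. ANOVA, Kruskal-Wallis test) and *post-hoc* tests to adjust for multiple comparisons". No error rate, significance level or rule for declaring an OTU is given.
- **Section 122 (sample size).** For the same split, the Wilcoxon-Mann-Whitney test is "applied to each OTU individually and the resulting *P*-values multiplicity adjusted with the Benjamini and Hochberg method to control the false discovery rate". The Figure 3 legend repeats this: "WMWavg refers to the Wilcoxon-Mann-Whitney test as applied to each OTU and multiplicity adjusted to control for false discovery rate". The alpha of 0.05 and the 80% power at 82 per group are stated for that procedure, and then "A sample size of $n = 100$ per group was selected".

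Section 122 also shows that its authors expected a correction across OTUs. It offers eight microbiome profiles as a simpler fallback, "rather than variability across 20 different OTUs/species, thus reducing the need for correction for multiple testing".

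For comparison, section 125 writes a false-discovery-rate adjustment directly into the gene-by-gene comparison of the microarray data.

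**The concern.** A post-hoc test is a second step after an overall test of three or more groups, and it protects the family of pairwise group contrasts within one outcome. In section 127 there are two groups and 20 outcomes, so the family that needs protection is the set of OTUs. No post-hoc group test touches that family.

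An analyst could therefore follow section 127 to the letter, report P values unadjusted across OTUs, and still be within the protocol. This is the first analysis listed for a primary objective. A taxon named as associated with IgA response could be a chance finding from 20 looks, while the power statement in section 122 would suggest that an adjusted procedure had been used.

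**Working it through.** **Inputs from the documents**

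- 20 OTUs, two groups (section 127).
- Alpha 0.05, 82 per group for 80% power, 100 per group selected (section 122). Section 127 gives no alpha, so 0.05 per OTU is borrowed from section 122.
- 1.5-fold difference in the 10 most abundant OTUs and 2-fold in the next 10, with 150 OTUs considered in the power simulation (section 122).

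**Step 1. The plan's own figure.** The 80% power comes from simulation on data built into an external application. The documents give no abundance distribution or SD, so it cannot be reproduced. The table assumes log-normal, independent abundances and shows average power over the 20 changed OTUs, with rank tests and Benjamini-Hochberg at 5%, 82 per group, 200 runs per cell:

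| Assumed log-SD | Adjusted over 20 OTUs | Adjusted over 150 OTUs |
|---|---|---|
| 0.8 | 94% | 82% |
| 1.0 | 85% | 64% |
| 1.1 | 77% | 55% |
| 1.4 | 60% | 31% |
| 2.0 | 25% | 6% |

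The stated 80% is attainable for some SD. It can be neither confirmed nor called wrong. The table also shows that the size of the family matters.

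**Step 2. What a post-hoc step does with two groups.** The number of pairwise contrasts among k groups is k(k-1)/2. For k = 2 this is 2 × 1/2 = 1, so there is nothing to adjust. In one generated data set of 100 v 100, the ANOVA, t-test and Tukey P values were all 0.0381.

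**Step 3. Error rate with no adjustment across OTUs.** With 20 independent tests at 0.05 and no true association:

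- P(at least one declared) = 1 - 0.95^20 = 1 - 0.3585 = 0.6415, or 64%.
- Expected number of false declarations = 20 × 0.05 = 1.0.

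**Step 4. Dependence between OTUs, and the effect of Benjamini-Hochberg.** Null simulations of the two-group Kruskal-Wallis test, 100 per group, 20 OTUs tested. Runs per setting: 4,000 independent, 3,000 equicorrelated, 1,500 compositional. The compositional data were Dirichlet-multinomial counts on 150 OTUs at four settings, with the 20 most abundant tested.

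| Data | At least one OTU, unadjusted | At least one OTU, Benjamini-Hochberg 5% |
|---|---|---|
| Independent | 64.9% | 4.9% |
| Compositional | 63.7% to 65.7% | 4.1% to 4.6% |
| Equicorrelation 0.1 | 63.8% | 4.8% |
| Equicorrelation 0.3 | 55.3% | 4.6% |
| Equicorrelation 0.5 | 43.4% | 4.2% |
| Equicorrelation 0.8 | 23.3% | 2.5% |

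The simulated 64.9% agrees with the analytic 64.15%: the Monte Carlo standard error is √(0.64 × 0.36/4,000) = 0.8 percentage points. When no OTU is truly associated, every declaration is false, so the false discovery rate equals the chance of at least one declaration. That is why Benjamini-Hochberg at 5% holds the last column at or below about 5%.

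**The case against.** The strongest reply is that the protocol, read as a whole, already answers the point. Section 127 says the step is meant to adjust for multiple comparisons, and with two groups the only multiplicity in that sentence is the OTUs. Section 122 names Benjamini-Hochberg for the same comparison, and the Figure 3 legend repeats it. On that reading, post-hoc is a loose phrase for an adjustment defined elsewhere, and the error rate is about 5%. The objective is also worded as exploration, and section 127 adds unsupervised clustering and regression, so no single OTU P value decides it.

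Much of this stands, and it rules out several stronger conclusions that a reader might draw.

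- *That the protocol has no multiplicity control for this comparison.* The documents do not support this. The intent is stated in section 127 and an adequate method is named in section 122.
- *That the planned test is a different one from the test that was powered.* For the rank-based option this is not so. With two groups, Kruskal-Wallis is the two-sided Wilcoxon-Mann-Whitney test in its large-sample form. The gap is the missing adjustment, together with ANOVA being left open as an alternative.
- *That the error compounds further because nasal and oral IgA are both tested.* Section 127 speaks only of mucosal IgA responders and does not say that two definitions are tested separately. Any figure would need an agreement rate that the documents do not give.

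The reply does not remove the gap. A sample-size assumption is not an analysis instruction. Where this protocol wants false-discovery-rate control in an analysis, as in section 125, it says so. Section 127 names something else, and that something does not do the stated job. The exploratory wording carries limited weight for an analysis that serves a primary objective and for which power was claimed.

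**Conclusion.** The point holds as a mismatch between the analysis text and the procedure on which the sample size rests. Section 127 states the right aim, names a device that cannot meet it with two groups, and leaves out the Benjamini-Hochberg step in section 122.

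The cost of a literal reading is a chance of about 64% of declaring at least one OTU when none is associated, against at most about 5% with Benjamini-Hochberg. The 64% rests on three conditions: no adjustment across OTUs, 0.05 per OTU, and near-independent OTUs. The compositional simulations stayed close to it. Strong positive correlation lowers it, yet at equicorrelation 0.8 it is still 23%, more than four times the nominal 5%. It is not a forecast of what the trial will do, since an analyst who takes the method from section 122 avoids it. Nothing here shows that the stated power or sample size is wrong.

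**What to change.** In section 127, replace the ANOVA, Kruskal-Wallis and post-hoc wording with text to this effect: for each IgA responder definition, the relative abundance of each tested OTU will be compared between responders and non-responders with a two-sided Wilcoxon-Mann-Whitney test (equivalently, two-group Kruskal-Wallis); P values will be adjusted by Benjamini-Hochberg at 5% across the tested OTUs; an association will be claimed only for OTUs that pass.

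Two details need stating with it.

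- **The family.** Say whether it is the 20 OTUs of section 127 or the 150 considered in section 122, and which of the two the power calculation adjusted over.
- **Nasal and oral IgA.** Say which measure defines a mucosal responder, or that both are analysed. Adjusting jointly over both is optional, but it should not be described as the procedure that was powered, because section 122 describes a single responder split.

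The cost is a sentence or two in the analysis text. The downside is that fewer OTUs will be declared. The stated 82 and 100 per group already assume the Benjamini-Hochberg adjustment, so they need not change on this account, provided the family is no larger than the one used in the power calculation.
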